## Abstract

**Background:**

Adolescents at risk for substance misuse are rarely identified early due to existing barriers to screening that include the lack of time and privacy in clinic settings. Games can be used for screening and thus mitigate these barriers. Performance in a game is influenced by cognitive processes such as working memory and inhibitory control. Deficits in these cognitive processes can increase the risk of substance use. Further, substance misuse affects these cognitive processes and may influence game performance, captured by in-game metrics such as reaction time or time for task completion. Digital biomarkers are measures generated from digital tools that explain underlying health processes and can be used to predict, identify, and monitor health outcomes. As such, in-game performance metrics may represent digital biomarkers of cognitive processes that can offer an objective method for assessing underlying risk for substance misuse.

**Objective:**

This is a protocol for a proof-of-concept study to investigate the utility of in-game performance metrics as digital biomarkers of cognitive processes implicated in the development of substance misuse.

**Methods:**

This study has 2 aims. In aim 1, using previously collected data from 166 adolescents aged 11-14 years, we extracted in-game performance metrics from a video game and are using machine learning methods to determine whether these metrics predict substance misuse. The extraction of in-game performance metrics was guided by literature review of in-game performance metrics and gameplay guidebooks provided by the game developers. In aim 2, using data from a new sample of 30 adolescents playing the same video game, we will test if metrics identified in aim 1 correlate with cognitive processes. Our hypothesis is that in-game performance metrics that are predictive of substance misuse in aim 1 will correlate with poor cognitive function in our second sample.

**Results:**

This study was funded by National Institute on Drug Abuse through the Center for Technology and Behavioral Health Pilot Core in May 2022. To date, we have extracted 285 in-game performance metrics. We obtained institutional review board approval on October 11, 2022. Data collection for aim 2 is ongoing and projected to end in February 2024. Currently, we have enrolled 12 participants. Data analysis for aim 2 will begin once data collection is completed. The results from both aims will be reported in a subsequent publication, expected to be published in late 2024.

**Conclusions:**

Screening adolescents for substance use is not consistently done due to barriers that include the lack of time. Using games that provide an objective measure to identify adolescents at risk for substance misuse can increase screening rates, early identification, and intervention. The results will inform the utility of in-game performance metrics as digital biomarkers for identifying adolescents at high risk for substance misuse.

**International Registered Report Identifier (IRRID):**

DERR1-10.2196/46990

## Introduction

### Background

Despite existing evidence-based interventions, many adolescents continue to misuse substances [1]. In 2021 alone, over 1 in 5 adolescents aged 12-17 years misused substances (illicit drugs and alcohol or tobacco products) [2] and 2 million adolescents had a substance use disorder [2]. Adolescent substance misuse, defined as “the unhealthy use of alcohol or drugs to relieve stress, alter reality or bring about pleasure” [3], increases the risk of developing a substance use disorder. Adolescents with substance use disorders are more likely to engage in criminal activity, contract sexually transmitted infections, develop comorbid mental disorders, and die early [4]. In addition, between 2019 and 2020, there was a 44% increase in drug-involved deaths among adolescents aged 10-19 years [5]. The negative consequences arising from substance misuse underscore the need to identify at-risk adolescents early to deliver timely prevention and treatment interventions.

Less than 10% of adolescents in need of substance use treatment receive it [6] in the setting of poor screening uptake and referral for treatment [7]. Many adolescents with substance misuse are not identified early, and barriers in screening adolescents for substance misuse contribute to this. The American Academy of Pediatrics and the Substance Abuse and Mental Health Services Administration recommend universal screening to identify at-risk adolescents. Yet, fewer than half of primary care providers [8] and fewer than a fifth of School-Based Health Center providers [9] screen adolescents for substance misuse [8,9]. Identifying at-risk adolescents early and delivering effective prevention interventions can prevent substance misuse-associated morbidity and mortality [10,11]. Barriers to screening adolescents for substance misuse include the lack of time, concern that adolescents will not be forthcoming about misuse, discomfort with conducting screening, and difficulty with providing a confidential space to conduct screening [8,12-15]. Innovative solutions that address or mitigate these barriers and lead to early identification of at-risk adolescents are urgently needed.

Digital tools hold great potential to mitigate identified barriers in screening for substance misuse given the ubiquity of mobile devices. These digital tools can be accessed anywhere and include mobile phones, wearables such as smart watches or Fitbits, mobile or web-based apps, and game software. Serious games—“games designed for a primary purpose other than play” [16]—are frequently used by over 95% of adolescents [17]. Serious games are increasingly being used for delivering health interventions among adolescents [18,19] and, more recently, are also being used for assessment of mental health outcomes [20,21]. During gameplay, in-game metrics reflective of performance in the game are being collected by the game software [18,22]. These metrics may reflect digital biomarkers of health outcomes [22].

Digital biomarkers are “consumer-generated physiological and behavioral measures collected through connected digital tools that explain, influence or predict health-related outcomes” [22,23]. Although most studies investigating the utility of digital biomarkers for health screening and monitoring have focused more on data collected from mobile phones [24,25] and wearables [26,27], games offer another source of data that could potentially measure digital biomarkers [22]. In-game performance metrics [18], such as the amount of time to complete a game task, accuracy of choices in a game task, or style of gameplay (ie, choosing a game task without attention to outlined rules), may reflect cognitive processes such as working memory, processing speed, and inhibitory control [22]. These cognitive processes (working memory and inhibitory control) affect in-game performance and can therefore be measured using in-game performance metrics [28,29]. Deficits in working memory [30,31] and inhibitory control [32] are also associated with substance misuse among adolescents [33] and may explain by up to 33% of the variance in future risk of substance misuse [33]. As such, in-game performance metrics may reflect digital biomarkers of cognitive function, which may be used in predicting adolescents at risk for substance misuse. Digital biomarkers have been used to predict health risk among adults [34,35] and adolescents [25,27]. Prior studies have also investigated the utility of digital biomarkers for a range of psychiatric disorders [24,26,34,36,37]. In these studies, the digital biomarkers captured were primarily from phone or wearable sensors and included measures such as movement, location, sleep, heart rate, and social interaction through call or text logs [24-27,34,37]. Although games are increasingly being used for measuring health outcomes such as cognitive function [38], their utility as digital biomarkers is yet to be widely investigated. In addition, all of the studies that have investigated the utility of game-based digital biomarkers have focused on adults [21,39,40]. A study by Dechant et al [39] demonstrated that participants with social anxiety exhibited in-game behavior that was different compared to participants without social anxiety. Specifically, participants with social anxiety were more likely to have their avatar stand at a larger distance to nonplayer characters in the game. In another study by Gielis et al [40], they investigated the utility of in-game performance metrics to identify adults with mild cognitive impairment (MCI). Adults identified as having MCI took more time to think about a move and made more errors in the game compared to adults without MCI.

To the best of our knowledge, we are not aware of any studies that have investigated the utility of game-based digital biomarkers for adolescent substance misuse. Given the easy access to games and the high level of motivation and engagement with games among adolescents [17,41,42], game-based digital biomarkers hold promise for risk identification among adolescents. The use of games as a screening tool could also mitigate barriers in screening since these games can be deployed without supervision and can be completed in private. In addition, prior studies have indicated that adolescents are more forthcoming when completing digital screeners compared to provider interviews and prefer this form of screening [43]. Finally, future apps of game-based screening and monitoring tools could integrate with the electronic health record to make results readily accessible to providers.

### Study Objectives

This paper describes the protocol for a proof-of-concept study to develop and test a predictive model for identifying adolescents at risk for substance misuse using in-game performance metrics. The primary objective of this study is to identify game-based digital biomarkers of cognitive risk factors implicated in the development of substance misuse among adolescents using available in-game performance metrics from an existing serious video game intervention, *PlayForward: Elm City Stories*, developed by the play2PREVENT Laboratory in partnership with Schell Games (hereafter referred to as *PlayForward*) [19].

## Methods

### Overall Study Design

The purpose of this pilot study is to identify game-based digital biomarkers of cognitive risk factors implicated in adolescent substance misuse by developing and testing a machine learning predictive model. This study is led by a team with expertise in machine learning, game design, cognitive function, adolescent substance misuse, and the conduct of pilot trials. This study’s team demonstrates a team science approach to solving public health problems with investigators from Yale University, Carnegie Mellon University, and International Business Machines Corporation.

### Aim 1

#### Objective

The objective of aim 1 is to identify game-based digital biomarkers of adolescent substance misuse.

#### Overall Study Design of Aim 1

Using data collected in a previous study [19], we will determine specific in-game performance metrics—digital biomarkers—that more strongly associate with a high risk for substance misuse. Adolescents will be grouped in 2 groups—high and low risk for substance misuse—based on their baseline responses to questions about substance misuse behaviors (eg, “in the past 30 days, have you used cannabis?” and “How sure are you that you can refuse if a friend offers you alcohol and you do not want it?”). We will have 2 prediction tasks (substance misuse and self-efficacy to refuse drugs). For each task, we will identify an effective prediction model by testing 6 machine learning classification models (eg, logistic regression, random forest, decision trees, support vector machine, gradient boosted decision tree, and neural networks). We will assess the feasibility of using a logistic regression model to compute a digital biomarker score for each adolescent that ranges from 0 to 1, where an adolescent with a higher score has a higher substance misuse risk.

#### Data Source

*PlayForward* is an evidence-based video game intervention developed in the play2PREVENT laboratory for HIV prevention and reduction of high-risk behaviors such as substance misuse [18,19,44,45]. *PlayForward* includes 12 Challenge Stacks or levels (the narrative and story-based components of the game) and 5 minigames (People Sense, Refusal Power, Me Power, Priority Sense, and Know Sense). Each of the minigames has 10 levels. The minigames are designed to help the adolescent develop and practice adaptive skills—such as learning to say no to an invitation to use drugs—that can be translated into real life. Players earn stars and points during gameplay, which allow them to advance in the game. *PlayForward* was tested in a randomized controlled trial of 333 adolescents, aged 11-14 years, where 166 adolescents were assigned to play the *PlayForward* video game [19]. At baseline, self-report data on substance misuse and self-efficacy to refuse drugs were collected. During gameplay, data related to their performance in the game (Table 1) were collected by the game software and later stored as log files. The game developers (Schell Games) developed reference files for decoding information stored in the log files.

**Table 1 table1:** Potential in-game biomarkers.

Minigame or subsection of minigame		Potential in-game biomarkers		Hypothesized neurocognitive domains (DSM-5^a^)
**People sense**				
	Deciding friends: checking out each person’s information	Time spent checking peer’s characteristics Correctly sorting peers into the right social or friendship circles Time spent completing social or friendship circles	Working memory, attention, inhibitory control, and processing speed Working memory and decision-making Working memory and processing speed	
	Accepting or rejecting invites	Correctly accepting or declining invitations based on risk and social circles Proportion of accepted unsafe invitations	Working memory, decision-making, and judgement Decision-making, and judgement	
**Refusal power**				
	Think	Correctly identifying the type of peer pressure	Decision-making and inhibitory control	
	Prepare	Correctly choosing reasons to say no	Decision-making and inhibitory control	
	Refuse	Time spent completing the sentence portion of minigame	Working memory and processing speed	
Priority sense		Number of times priority dropped to zero		Working memory
Know sense		Total credibility score at the end of the minigame		Working memory, decision-making, and processing speed

^a^DSM-5: Diagnostic and Statistical Manual, 5th Edition.

#### Data Extraction and Analysis

Three authors (KA, [name], and [name]) played the *PlayForward* game and reviewed the literature and gameplay guides for *PlayForward* to identify in-game performance metrics that likely used cognitive function and could therefore be potential in-game digital biomarkers of cognitive function (Table 1). We have identified 285 in-game performance metrics (eg, the number of times the player lost the minigame; Multimedia Appendix 1). One of the authors (SK) extracted all identified in-game performance metrics from log files into a CSV file and uploaded this into R statistical software (R Foundation for Statistical Computing) [46]. In-game performance metrics that are found to predict substance misuse risk following analysis will be identified as digital biomarkers for adolescent substance misuse risk.

In total, 2 outcomes (described in the assessments section below)—substance misuse and self-efficacy—to refuse drugs will be used in 2 prediction models. Based on adolescent baseline response to questions on substance misuse and self-efficacy to refuse drugs in a previous study [19], a substance misuse score and self-efficacy to refuse drugs score have been derived. For each score, adolescent participants are categorized into 2 groups (high risk and low risk) based on the score distribution. A preliminary examination of the log files of the 166 participants who played the *PlayForward* game resulted in dropping 6 log files due to file errors. As such, analysis of aim 1 will occur with a final sample of 160 participants.

#### Outcome Measures

##### Substance Misuse

In total, 20 questions on cigarette, alcohol, and drug use behaviors from the Youth Risk Behavior survey [47] were administered to 11- to 14-year-old adolescents in the *PlayForward* randomized controlled trial at baseline [19].

Questions included whether participants had ever tried using cigarette, alcohol, or other drugs (marijuana, cocaine; inhalants; over-the-counter drugs; and nonprescribed prescription drugs such as opioids, methamphetamines, and injection drugs); substance use in the previous 30 days; and age at first use (for cigarette and alcohol).

In total, 15 questions on ever use and past 30-day use (for substances other than alcohol or cigarette) had options of yes, no, and decline to answer. In total, 2 questions on age at first use (for cigarette and alcohol) had 9 options: “I have never smoked a whole cigarette/I have never had a drink of alcohol other than a few sips”; 8, 9, 10, 11, 12, 13, and 14 years or older; and decline to answer. Further, 1 question on past 30-day use of cigarettes had 8 options: I did not smoke cigarettes during the past 30 days, less than 1 cigarette/day, 1 cigarette per day, 2-5 cigarettes/day, 6-10 cigarettes/day, 11-20 cigarettes/day, more than 20 cigarettes/day, and decline to answer. Furthermore, 1 question on past 30-day use of alcohol had 8 options: 0 days, 1 day, 2 days, 3-5 days, 6-9 days, 10-19 days, 20 or more days, and decline to answer.

In addition, if participants answered “no” to a particular question about having ever used cigarette or alcohol or drugs, they skipped subsequent questions about past 30-day use and age at first use (for cigarettes and alcohol). A participant could skip up to 9 questions.

##### Coding

For this age group, we considered any type of substance misuse to be high risk. As such, if any adolescent answered “yes” to any of the above questions, we coded them as high risk. Based on this criterion, 107 (66.9%) of 160 adolescents were low risk because they answered “no” to all the substance misuse questions.

##### Self-Efficacy to Refuse Drugs

In total, 10 questions from the Drug Use Resistance Self-Efficacy [48] scale were used to calculate a score. The Drug Use Resistance Self-Efficacy scale asks questions relating to confidence in one’s ability to refuse drugs in a variety of situations. The options to each question include “not sure at all,” “not very sure,” “pretty sure,” and “definitely sure.” Each option was recoded as follows: “definitely sure”=0, “pretty sure”=1, “not very sure”=2, and “not sure at all”=3. As such, scores could range from 0 to 30, and higher scores meant lower self-efficacy to refuse drugs. In this sample of 160 adolescents, scores ranged from 0 to 27 with a mean of 2.38 (SD 4.40). Adolescents were grouped into 2 groups (high risk and low risk) based on the score distribution. Adolescents with a total score of 0 were considered low risk (n=82, 51.2%), whereas adolescents with a total score greater than 0 were considered high risk (n=78, 48.8%).

#### Analyses

Machine learning models [49] will be used to predict each outcome. We will use k-fold cross-validation [50] to evaluate the performance of 6 machine learning classification models (logistic regression, random forest, decision trees, support vector machine, gradient boosted decision trees, and neural networks) to predict each of the outcomes. These 6 models are representative of a range of popular classification models that have been previously used in substance use research [51]. These models vary in their underlying mathematical approaches and often offer reasonable to good performance across a variety of data sets. For example, while regression models are easy to implement, the underlying assumption is that predictors are independent [51]. Decision trees on the other hand do not require elaborate preprocessing but perform relatively worse than other models [51]. Support vector machine performs well using unstructured data but requires extensive tuning [51]. The primary evaluation metric used will be the area under the receiver operating characteristic (AUROC) curve [50]. For each outcome, the model with the AUROC value closest to 1 is the one that has the best ability to discriminate between risk classes, across all classification threshold levels ranging from 0 to 1 [50]. Ideally, an AUROC value of greater than 0.7 can be achieved by the best model. We will also report the sensitivity and specificity for a range of classification thresholds. In the event that AUROC values are similar across candidate models, it may be useful to identify the best model as the model that offers the most appropriate trade-off between sensitivity and specificity, even if the AUROC value of that model may not be the highest [50,52]. Existing screening tools for substance use have sensitivity ranging from 0.71 to 0.94 and specificity ranging from 0.87 to 0.97 [53,54]. As such, to identify an adolescent at risk for substance misuse, we want to achieve comparable sensitivity and specificity above 0.7. Given the risk of negative outcomes such as an overdose that can occur with adolescent substance misuse, a model that produces a higher sensitivity compared to its specificity would be consistent with existing recommendations for substance use screening tools [53]. For the best model identified for each outcome, we use Shapley additive explanations [55,56] to explain the relative importance of the features used to predict the outcome class (ie, high risk vs low risk). We will define features (ie, predictor variables used to inform the classification) from in-game performance metrics. When selecting features to be used for classification, the variance threshold method will be used to remove features with 0 (or low) variance because they are unlikely to be useful for discriminating between classes [49]. We will reduce multicollinearity between features by selectively removing a subset of highly correlated features before performing classification [49]. In addition, we will assess in-game metrics for multicollinearity and drop in-game performance metrics with a variable inflation factor larger than 10 [57].

### Aim 2

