#### Participants and Source

Adolescents from 1 to 3 Connecticut high schools will be recruited. To be eligible for this study, participants must (1) attend a high school in Connecticut, (2) be aged between 14 and 15 years, (3) be willing to sit for 60 minutes per session to play the game, and (4) be able to provide assent and parental or guardian consent. Following screening, eligible adolescents who provide parental consent and assent will complete baseline assessments. Adolescents who complete baseline will be grouped into high-risk and low-risk groups based on their response to assessment of substance misuse, depression, and anxiety. High risk will be determined using their report at baseline of monthly use of any substance (alcohol, tobacco, marijuana, prescription drugs, inhalants, illegal drugs, and synthetic drugs), a score of >2 on the Patient Health Questionnaire-2 [58], and a score of >2 on the Generalized Anxiety Disorder 2-item scale [59]; low risk will be determined by no substance use in the past year, <2 on the Patient Health Questionnaire-2, and <2 on the Generalized Anxiety Disorder 2-item scale. We chose a higher age range (14-15 y) for aim 2 (in contrast to the age range of 11-14 y in aim 1) to ensure that we can recruit a high-risk sample (adolescents with substance misuse).

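### Aim 1 judges game metrics against substance use reported before play without an age-only benchmark, so an AUROC near 0.7 would not by itself show that the metrics add anything to age

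*Protocol article*

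**What the plan says.** All references are to the protocol article.

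- **Predictors.** Aim 1, Analyses: "We will define features (ie, predictor variables used to inform the classification) from in-game performance metrics". Aim 1 names no age feature, stratum, adjustment or reference model.
- **Outcome.** Under Substance Misuse: "Questions included whether participants had ever tried using cigarette, alcohol, or other drugs". A participant who denied ever using a substance skipped the later questions on it, so the ever-use items largely determine the class. Coding then states: "For this age group, we considered any type of substance misuse to be high risk". The resulting split is "107 (66.9%) of 160 adolescents were low risk".
- **Timing.** Data Source: "At baseline, self-report data on substance misuse and self-efficacy to refuse drugs were collected", and then "During gameplay, data related to their performance in the game (Table 1) were collected by the game software and later stored as log files". The class was fixed before any metric was recorded.
- **Success and labelling.** Analyses hopes for an AUROC above 0.7 from the best model, with sensitivity and specificity also above 0.7. Data Extraction and Analysis says that metrics found to predict misuse risk will be identified as digital biomarkers of that risk.
- **Age and use.** Participants and Source: "We chose a higher age range (14-15 y) for aim 2". The reason given is to be sure of recruiting adolescents who misuse substances.
- **Second task.** Aim 1 also classifies low versus high self-efficacy to refuse drugs, again from baseline answers and again without an age reference.

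**The concern.** Any-lifetime-use status can move in only one direction as a child gets older. The sample covers four years of age, and the protocol relies on older adolescents having more users when it plans Aim 2. If game performance also changes over ages 11 to 14, which is plausible but not stated in the document, a classifier given only game metrics can gain discrimination by picking up age. An absolute AUROC target cannot separate that from information specific to the metrics. Age is known without playing a game that takes about six one-hour sessions, so a metric that merely stands in for age has little value as a screening measure. It would also be a doubtful biomarker of the cognitive risk factors named in Study Objectives.

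A second, smaller issue is wording. The class was reported before play, and the Abstract accepts that misuse may itself influence game performance. The analysis can show that metrics distinguish adolescents who have already reported use. It cannot show that they foretell the development of misuse. The limitations in the Discussion mention neither age nor the timing of the outcome.

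**Working it through.** **1. The plan's own figure.** 107/160 = 66.9% low risk, as stated. That leaves 160 − 107 = 53 high risk, or 33.1%.

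**2. Age-only AUROC.** The article gives the age range but no age mix and no use by age, so the following are assumptions: equal shares at ages 11, 12, 13 and 14; a logistic relation between age and use; overall prevalence fixed at 53/160. The odds ratio (OR) per year of age is varied. With p(a) the probability of use at age a, and ties counted as one half,

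AUROC = Σₐ P(age = a | user) × [P(age < a | non-user) + ½ P(age = a | non-user)].

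| Assumed OR per year | Use at 11 / 12 / 13 / 14 | Age-only AUROC |
|---|---|---|
| 1.25 | 26.0 / 30.5 / 35.4 / 40.7% | 0.57 |
| 1.5 | 20.7 / 28.1 / 37.0 / 46.8% | 0.62 |
| 2.0 | 13.7 / 24.1 / 38.8 / 55.9% | 0.70 |

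Worked line for OR 2.0. The age shares among users are 0.103, 0.182, 0.293, 0.422; among non-users they are 0.323, 0.284, 0.229, 0.165. The four terms are 0.017 + 0.084 + 0.211 + 0.387 = 0.70.

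A different age mix (0.2/0.3/0.3/0.2) with assumed use of 15/25/40/55% gives prevalence 0.030 + 0.075 + 0.120 + 0.110 = 33.5%, and an age-only AUROC of 0.67.

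**3. A single metric linked to use only through age.** By simulation under the equal age mix, for assumed correlations of the metric with age of 0.3 / 0.5 / 0.7:

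- OR 1.25: AUROC 0.52 / 0.54 / 0.55
- OR 1.5: AUROC 0.54 / 0.56 / 0.59
- OR 2.0: AUROC 0.56 / 0.60 / 0.65

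A model that combines many such metrics can move towards the age-only value, but not beyond it except by chance.

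**4. Precision at 53 versus 107.** Hanley-McNeil with A = 0.70: Q₁ = A/(2 − A) = 0.538; Q₂ = 2A²/(1 + A) = 0.576.

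SE² = [0.70 × 0.30 + 52 × (0.538 − 0.49) + 106 × (0.576 − 0.49)]/(53 × 107) = 11.90/5671 = 0.00210 (unrounded Q values used), so SE = 0.046.

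The 95% interval is 0.70 ± 1.96 × 0.046, about 0.61 to 0.79. The age-only values for ORs of 1.5 and 2.0 (0.62 and 0.70) lie inside it; the value for 1.25 (0.57) lies just below it.

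**5. Precision of the gain.** If both AUROCs have an SE of 0.0458 and correlation ρ, the SE of their difference is 0.0458 × √(2(1 − ρ)). An assumed ρ of 0 gives 0.065 (half-width 0.13); an assumed ρ of 0.5 gives 0.046 (half-width 0.09). A gain of a few hundredths would be inconclusive.

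**The case against.** The strongest reply is that the age gradient is assumed. Choosing 14- to 15-year-olds for Aim 2 implies more use in an older group; it does not establish a gradient within ages 11 to 14. This stands. Age alone reaches 0.70 only if the odds double per year, and weaker gradients fall short. Nor does age easily meet the second target. In the 15/25/40/55% scenario, a cut at age 13 or above has sensitivity (0.120 + 0.110)/0.335 = 0.69 and specificity (0.170 + 0.225)/0.665 = 0.59. A cut at age 14 has 0.33 and 0.86. These are reasons to measure the age effect, not grounds for assuming it is absent.

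It may also be said that a condensed article can leave comparator models to a fuller plan, and that the quoted sentence does not forbid one. That is fair as far as it goes. But the article does fix the feature source, the absolute target and the rule that turns a predictive metric into a biomarker, and those three together create the problem.

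Three stronger readings are tempting but unsupported:

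- **That the metrics are merely age markers.** The document gives neither the relation of the metrics to age nor that of age to use.
- **That age would reverse the Aim 2 hypothesis.** A reader might reason that older players play better and use more, so the score would rise with cognition. Every link in that chain is outside the document.
- **That Aim 1 supports no risk claim at all.** The plan openly groups adolescents by baseline answers and compares itself with existing screening tools. Concurrent screening remains a legitimate claim, and in that setting predict is ordinary classifier language.

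The accumulation argument also does not cover the self-efficacy task, whose score reflects current confidence.

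**Conclusion.** The point holds in limited form. For the substance misuse task, an AUROC near 0.7 without an age reference would not establish that the game metrics carry information beyond age, and so would not justify the unconditional biomarker label. The possible contribution of age ranges from small (0.57) to the whole of the target (0.70) over assumed odds ratios of 1.25 to 2.0 per year, with a standard error of about 0.046 around an observed 0.70. The size rests on the assumed age mix and gradient; the document cannot settle it. What is certain is that the outcome includes lifetime use, was reported before play, and is to be predicted from game metrics with no age comparator stated. The supportable conclusion from Aim 1 is concurrent classification of use already reported. This should be changed, but it does not invalidate the study.

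**What to change.** 1. In the same cross-validation folds, fit an age-only model, adding sex if the earlier trial's data include it. Report its AUROC, the AUROC of age plus game metrics, and the gain with a confidence interval.
2. Describe metrics as biomarkers only to the extent that they add to age, and say that this gain may be imprecise with 160 participants.
3. Report the same benchmark for self-efficacy, for consistency.
4. Word the Aim 1 conclusion as concurrent classification of use already reported, not as prediction of later misuse, and add age and outcome timing to the limitations.

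Adjusting the Aim 2 correlations for age is not a substitute. Any influence of age would sit in the weights trained in Aim 1, and a sample of 30 aged 14 to 15 cannot undo it.

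The cost is one additional model per task and some rewording. No new data are needed if individual ages from the earlier trial can be linked to the log files, which is assumed here. The downside is that the gain may be smaller than the raw AUROC suggests; if the age effect proves weak, the benchmark strengthens the case for the metrics.
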